#### Safety and Adverse Events

When safety guidelines are followed, tDCS is considered a safe stimulation modality for children and adolescents as well as for adult patients with various neurological conditions and healthy subjects, as studies prove in over 18,000 tDCS sessions in total (91). In addition, the lack of reported serious adverse events, also feasibility, tolerability and safety of tDCS in children and adolescents were positively evaluated (53, 58, 92). The mild and transient, reported adverse effects of tDCS in children and adolescents included tingling (11.5%), itching (5.8%), redness (4.7%) and scalp discomfort (3.1%) were similar to those in adults (93). For the reporting of any possible adverse effect, the German version of the questionnaire of sensations related to transcranial electrical stimulation is used (accessible at: http://neurologie.uni-goettingen.de/downloads.html). Unlikely events such as serious adverse events or adverse reaction related to the device will be reported to the Ethics Committee of the Medical University of Vienna, as well as to the Austrian Agency for Health and Food Safety (AGES). Nevertheless, as tDCS is a non-invasive method and free from major side effects, no serious health risks for the adolescent study participants of this study are expected. In the same vein, MRI measures are non-invasive and safe as long as the necessary precautions are followed; bearing no expected health risks for the examined study participants.

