### Transcranial Direct Current Stimulation and Its Application in Psychiatric Disorders

Transcranial direct current stimulation (tDCS) is a non-invasive brain stimulation technique that uses low intensity currents (~1–4 mA) to reduce or enhance neuronal activity (29) by generating electric fields (30). In tDCS, the current flux is unidirectional and passed by a pair or set of electrodes with a determined electrode polarity, the so-called anodal or cathodal tDCS. This current direction is thought to induce polarity-dependent effects on neuronal excitability, being highly dependent on the network state of the target area (31). Concluding from stimulation of the primary motor cortex and its after-effects, reflected by the amplitude changes of motor evoked potentials, anodal tDCS increases and cathodal tDCS decreases cortical excitability (31). tDCS is also able to alter brain connectivity and thus likely modulate neural communication (32). Studies using resting-state functional magnetic resonance imaging (fMRI) demonstrated the ability of tDCS to alter functional connectivity of the motor and pre-frontal cortex, fronto-parietal and default-mode network (33, 34). Moreover, direct currents were demonstrated to influence ongoing oscillatory activity in several canonical electroencephalographic (EEG) bands such as theta, alpha, beta and gamma (35, 36). Thus, tDCS was reported to lead to acute changes in brain activity, as the neuromodulatory effects begin within seconds after the stimulation starts. On the other hand, physiological aftereffects of tDCS can last for several hours and days (37, 38) and repeated tDCS sessions can even lead to long-term effects via cumulative neuroplastic changes (39).

In the treatment of psychiatric disorders, several brain stimulation techniques are used. More invasive techniques such as electroconvulsive therapy (ECT) are highly effective for severe major depression disorder, but require a sedation of the participant and often have persistent side effects such as cognitive impairment (40). Transcranial magnetic stimulation (TMS), which induces electric current by an electromagnetic field, is less invasive and commonly used in the treatment of depression; side effects are milder but comprise the risk of seizures (40, 41).

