Encouraging results from studies in adults with psychiatric disorders are driving research into non-invasive brain stimulation (NIBS), particularly TMS and tDCS, in children and adolescents (51). Reviews report feasibility and promising efficacy of these stimulation techniques in various neurologic and psychiatric disorders in children and adolescents such as ASD, ADHD, epilepsy, depression, dyslexia, cerebral palsy and Tourette syndrome (51–53). TDCS proofed to be safe and well-tolerated in this age group. However, up to 2021, no studies with anxiety or conduct disorders were reported in the tDCS adolescent literature.

As a pediatric population might have accelerated neural plasticity after brain stimulation (54), an even greater effect on plasticity after NIBS is expected in children and adolescents. However, regarding the effects and possible side effects on the developing brain, extreme carefulness is warranted when treating this population. Moreover, the immature brain has to be considered as a unique physiological entity, as results from translational studies are missing (52, 55, 56).

Besides the reported literature gap regarding tDCS studies in adolescents with depressive, anxiety or conduct disorders, limitations of previous clinical tDCS studies included missing control groups, insufficient stratification and randomization, the exclusion of female patients, small sample sizes or only unimodal outcome measures (i.e., no psychophysiological or behavioral measures, but solely clinical disorder-specific self-reports) (53, 57, 58).

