### Procedure and Intervention

After study inclusion, stratification and randomization, pre-measures including psychological questionnaires (first visit date), behavioral tests (second visit date) and fMRI paradigms (third visit date) will be conducted. Then, one of the two brain stimulation interventions (real or sham stimulation) will be conducted with each of the participants. In the beginning of every session, the participants will sit down on a chair and complete a brief questionnaire about their general wellbeing, attention, motivation and other life aspects (short mood questionnaires). Afterwards, an electrode stimulation cap will be placed on the head of the participant. Then, the treatment condition is initiated: either real transcranial direct current stimulation (experimental group) or sham (placebo) stimulation (control group). Both brain stimulation interventions will comprise 10 sessions on consecutive days (except weekends), as it was previously done in different successful tDCS treatment trials [summarized in (39)]. After the interventions, the same tasks as for the pre-measurement will be conducted for post-measurements. Follow-up measures, one, respectively, 3 months after the stimulation intervention, will similarly include all tasks as the pre-/ post measurement, except MRI measures.

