### Outcomes

The primary outcome of this study is the change in emotion regulation ability, measured by the raw score of the FEEL-KJ (74). Here, we expect an increase in emotion regulation after the intervention of the experimental group in total (as well as for each clinical experimental subgroup) compared to the control group in total (as well as for each clinical control subgroup).

As exploratory outcomes, we will investigate if the application of tDCS improves the disorder-related clinical symptomatology, quality of life or emotion regulation, whereas changes in raw scores of the related self- and parental reports (as summarized in Psychological Self- and Parental Ratings) are defined as secondary endpoints.

Further we will explore if indices of emotion recognition [measured via Frankfurter Test and Training for Recognizing Facial Affect (FEFA II) and the Emotion Recognition Task (ERT)], and (implicit) emotion regulation (measured via eSTROOP) improve from before to after tDCS stimulation. In addition, measures of attentional bias [*via* Attentional Bias Task (ABT)] and working memory (*via* e n-BACK) will give insight regarding potential improvements in the related indices from before to after tDCS stimulation. Indices of each task (such as the number of correct behavioral assignments, commission, omission, reaction times, eye gaze fixation duration, pupil dilation, brain activation, brain connectivity) are summarized in Eye Tracking and Behavioral Measures and fMRI Procedure and Measures.

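### A stimulation-sensation questionnaire is the stated tool for every possible adverse effect, so delayed non-serious events have no stated route to being recorded and individual worsening is not summarised

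*Protocol article*

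**What the plan says.** Safety and Adverse Events (protocol article) names one instrument and gives it universal scope: "For the reporting of any possible adverse effect, the German version of the questionnaire of sensations related to transcranial electrical stimulation is used". It does not say when the form is given. The next sentence sets up a second route: "Unlikely events such as serious adverse events or adverse reaction related to the device will be reported to the Ethics Committee", and also to the national agency. The adverse effects that the section lists from earlier paediatric work are tingling, itching, redness and scalp discomfort.

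The Introduction section on tDCS in psychiatric disorders describes a wider range of effects. It says that "physiological aftereffects of tDCS can last for several hours and days (37, 38) and repeated tDCS sessions can even lead to long-term effects". For young people it expects a greater effect on plasticity and adds that "regarding the effects and possible side effects on the developing brain, extreme carefulness is warranted when treating this population". It also reports that no adolescent tDCS study in anxiety or conduct disorders was known up to 2021.

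Participants are followed beyond treatment. Procedure and Intervention says: "Follow-up measures, one, respectively, 3 months after the stimulation intervention, will similarly include all tasks as the pre-/ post measurement, except MRI measures". It also has a short wellbeing and mood questionnaire at the start of each session. Psychological Self- and Parental Ratings lists self and parent scales and an interview covering general psychopathology, depression, anxiety, impulsivity and aggression. Statistical Analysis compares these secondary endpoints with the approach used for the primary endpoint, whose time factor has two levels, before and after treatment. Outcomes introduces them by saying that "we will investigate if the application of tDCS improves the disorder-related clinical symptomatology, quality of life or emotion regulation".

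**The concern.** This is a stated choice of instrument, not silence that a fuller protocol might fill. The article hands all possible adverse effects to a form whose title limits it to what is felt from the stimulation. That matches the four local effects listed in the same section. It does not match effects that appear hours, days or months later, or effects that are not sensations.

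By the article's own account, this trial would give the first adolescent tDCS safety information for two of its three diagnostic groups. Its Discussion looks forward to offering a non-invasive treatment option if the trial succeeds. That conclusion needs harms to have been asked about in both arms beyond the sensations of stimulation, over the period for which participants are followed anyway.

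**Working it through.** The main question is one of fit, so I set the sections side by side and then check what 54 per arm could show.

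**Step 1: which kinds of event have a stated route?**

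| Kind of event | Stated route | Remaining gap |
|---|---|---|
| Local or felt, around a session | Sensation questionnaire | Timing not stated |
| Serious, or device-related reaction | Report to Ethics Committee and agency | Onward reporting; no enquiry described |
| Change in mood or wellbeing during the treatment period | Short questionnaire at each session | Not linked to safety; tied to the sessions |
| Worsening depression, anxiety, aggression or general psychopathology | Scales and interview at pre, post, 1 and 3 months | Compared as pre/post scores; not linked to safety; no between-arm analysis stated for 1 and 3 months |
| Delayed, non-serious, outside those scales | None stated | Whole category |

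The last row is the gap in recording. The row above it is a gap in summary: the data are collected, but individual worsening is not counted.

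**Step 2: why mean scores do not replace a count.** If a proportion p of an arm worsens by an amount d and the others do not change, the arm mean moves by p × d. At an assumed p = 5%, the shift is 0.05d. For one participant in 54 it is d/54, about 0.019d. A comparison of means can leave such deterioration invisible; a count of participants passing a set threshold would show it.

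**Step 3: what can 54 per arm show?** Stratification and Randomization allocates 18 of 36 in each of three diagnostic groups to each condition: 3 × 18 = 54, as the article states. The article gives no adverse-event rates, so the rates below are assumptions, and every event is assumed to be ascertained.

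- Upper limit after zero events (one-sided 95%): 1 − 0.05^(1/54) = 5.4%.
- Chance of at least one event on real stimulation, 1 − (1 − p)^54:

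| True rate p | Chance of at least one in 54 |
|---|---|
| 0.5% | 24% |
| 1% | 42% |
| 2% | 66% |
| 5% | 94% |

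- Power to compare arms (two-sided 0.05, normal approximation): Φ[(|p1 − p2| − 1.96·SE0)/SE1], with SE0 = √(2·p̄(1 − p̄)/54), p̄ the mean of p1 and p2, and SE1 = √((p1(1 − p1) + p2(1 − p2))/54). For 10% against 2%, SE0 = 0.0457 and SE1 = 0.0451, so Φ[(0.08 − 0.0896)/0.0451] = Φ(−0.21) = 42%. The same formula gives 41% for 15% against 5%, and 66% for 20% against 5%.

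The trial has a fair chance of seeing events at rates of 2% to 5%, provided that someone asks. It has little power to compare uncommon events, so a descriptive report by arm is the realistic aim.

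**The case against.** The strongest reply is that the plan already looks for harm in several places. Self and parent ratings and an interview are repeated up to 3 months. The secondary endpoints include indicators of aggression, depression and anxiety, and are defined as changes in raw scores. The interaction test has no direction, and post-hoc tests are planned to find one. Each session opens with a mood questionnaire and includes 20 minutes of debriefing. Serious and device-related events have their own route. The reply adds that an article may leave adverse-event windows, coding and tables to the full protocol or analysis plan.

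Most of this stands, and it rules out several stronger readings:

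- A reader might infer that psychiatric harms would go unrecorded or uncompared. The scales and the stated analysis contradict that.
- A reader might infer that the article itself names psychiatric harms of tDCS as plausible. It raises developing-brain side effects and lasting effects in general terms. Acute suicidality appears only as an exclusion criterion, and thoughts of death only as a symptom of depression.
- A reader might infer that the form cannot register a headache. Its items are not shown.
- A reader might try to compute the share of follow-up that the form covers. Its schedule is not stated, so no such figure can be supported.

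Two things remain. The sentence on the instrument is explicit, and its scope is wider than its title can carry. And none of the other channels described asks about a delayed, non-serious event outside the scales, or turns worsening on the scales into a safety result. Missing timing, coding or tables are not held against the article.

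**Conclusion.** The point holds in a limited form. The stated instrument fits local, transient effects and not the lasting or developmental effects that the article raises. A delayed, non-serious event outside the symptom scales has no stated route to being recorded, and individual deterioration on the scales is not summarised as a safety result.

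No figure in the article measures how many events would be missed. The 5.4% upper limit describes what 54 participants allow under full ascertainment; it does not measure the gap. The conclusion rests on reading the form's scope from its title, and on the article's description of the other channels being complete as to what is asked. It is a worthwhile, cheap improvement and not a threat to the primary analysis.

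**What to change.** In Safety and Adverse Events, keep the sensation form for the sessions and add:

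1. One open question on any new or worsened physical, mood or behaviour problem since the last contact, asked by blinded staff at each session, at the post-measurement, and at 1 and 3 months.
2. A descriptive report by arm of the adverse events so collected.
3. By arm, the proportion worsening from baseline by an amount fixed before unblinding on scales already collected (BDI, DISYPS-III, STAXI, YSR/CBCL), at post, 1 and 3 months.
4. One sentence saying how worsening on those scales feeds into safety reporting.

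Cost: no new visits or staff. There are 10 + 1 + 1 + 1 = 13 occasions; at an assumed two minutes each, that is 26 minutes per participant over the whole trial, plus a short safety table. Reported adverse-event rates will look higher than with the sensation form alone, in both arms, and comparison of uncommon events will stay imprecise. The table should therefore be labelled descriptive.

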### Instruments

To complement the determined, unimodal measure for the investigation of the primary hypotheses of this study, our study exceeds the typical outcome measures of tDCS studies (i.e., self-report-questionnaires) with a mix of methods on multiple levels will be applied before and after the therapeutic intervention for the remaining objectives of this study. Psychological self- and parental ratings will detect changes in emotion regulation, empathy, psychiatric symptoms and quality of life (multi-informant). Changes in behavioral reactions and gaze behavior will be measured with five computerized, psychological tasks. Neurophysiological changes in brain responses to emotional and cognitive stimuli will be examined with three fMRI paradigms. In addition, a resting-state MRI before and after the brain stimulation intervention will be used to gain insight into potential changes in brain functional connectivity.

#### Psychological Self- and Parental Ratings

To provide an integral view on the ability of emotion regulation, multi-informant assessment via children and parental ratings will be compiled. Further we aim to not only investigate the ability to regulate emotions and related emotion regulation strategies [via FEEL KJ / P: (74, 94), ERQ (95), ERC (96), ASQ-Y (97)] but also to detect difficulties in emotion regulation [via DERS (98)] and combine those indices to a holistic view on the individual's emotion regulation abilities. The FEEL questionnaire was selected as the primary outcome, as it provides not only a scale for adaptive and maladaptive strategies for emotion regulation, but more importantly, it provides the emotion regulation scores separately for three emotions, namely: anger, anxiety and sadness—mirroring the three- targeted clinical subgroups (conduct disorder, anxiety disorder and depressive disorders).

Multi-informant ratings and interviews will be also used regarding general psychopathology [YSR/CBCL, (99); Interview: KINDER DIPS (100)] and disorder-related symptoms and comorbidities, such as anxiety, depression, impulsivity and aggression [DISYPS III—SSV, DES, ANG, self- and parental rating versions (101), BDI (102), STAIK / STAI (103, 104), STAXI-2KJ / STAXI II (105, 106)].

We will also track possible changes in different aspects of empathy as a general supportive factor for emotion regulation [via IECA (107), ICU-C/P (108, 109), BES (110), GEM (111)], as well as quality of life as a proxy for treatment impact (96), with both self-report and parental questionnaires [KIDSCREEN (112)].

#### Eye Tracking and Behavioral Measures

##### Frankfurter Test and Training for Recognizing Facial Affect II

In this computerized task, the subjects have to identify basic emotions presented on 50 black and white photos of the entire face (113). The used stimuli are based on Ekman's concept basic emotions [happiness, sadness, anger, disgust, fear, surprise and neutral; (114)] and the test includes measurements of reaction times and correct classification.

##### Emotional Stroop Task

Here we adapt an emotional conflict task (implicit regulation), as prior used to detect the activation of medial pre-frontal regions during emotion regulation (115, 116). This paradigm is built as a variation of the STROOP task. Participants have to identify happy or fearful faces, and are instructed to ignore the overlaid words “fear” and “happy” (“ANGST” or “GLÜCK” in German) *via* button pressing. A trial-by-trial adaptation to emotional conflict brings up an emotional regulatory mechanism (116). Here, behavioral reactions (correct/incorrect classification, omission) will be recorded.

##### Emotional n-back Task

Cognitive and emotional capacities will be investigated using a modified version of a working memory n-back task (117) with emotional face stimuli pre and post brain stimulation intervention. This paradigm was developed as a modified emotional n-back task, which adopts to the current performance of the patient, varying the degree of difficulty adaptively during each stimulation session. During the task, behavioral reactions such as button presses (correct/ incorrect classification, omission) and reaction times will be recorded.

##### Attentional Bias Task

To investigate attentional bias, a static faces free-viewing task will be applied, where participants are instructed to observe the simultaneous presentation of a neutral facial expression and an emotional facial expression (angry, sad or happy faces). Changes in the direction of initial gaze, total fixation duration (118) and pupil dilation will be measured via eye tracking system (Tobii Group, Danderyd, Schweden).

##### Emotion Recognition Task

Emotions of different static and morphing faces displaying different emotional states will be presented to the participants to investigate the perception of emotions in others. The emotional stimuli will be taken from validated Databases [EU Emotion Stimuli Set (89); FACES Database (90)], and will be presented at pre and post measures. Besides behavioral reactions (correct/ incorrect classification, omission, reaction times), also gaze behavior, fixation duration and pupil dilation will be recorded via eye tracking system (Tobii Group, Danderyd, Schweden).

#### fMRI Procedure and Measures

MRI data will be acquired via a 3T Siemens MAGNETOM Prisma MR Scanner (Siemens, Erlangen, Germany) equipped with a 64-channel head coil. Sequence optimization will be conducted in accordance with the recommendations given by the Human Connectome Project (119) to allow for highly improved temporal and spatial resolution, leading to overall increased sensitivity and specificity for the subsequent analyses.

The subjects will first be explained the tasks and have trial runs outside of the scanning room. After a briefing on the correct behavior inside the gantry and a safety check, subjects will be transferred onto the scanner bed and placed in the MRI scanner. For task responses, subjects are given an MR-compatible button box (Current Designs Inc., [name]) which rests on their belly while in the scanner. The experimenters keep visual contact during the examinations and track the responses on the stimulus laptop. Stimuli are presented via a beamer and mirror system on a screen placed at the rear end of the gentry.

The MRI scans are planned in the following order: The e-nBACK is conducted first as it is expected to be the most cognitive demanding task followed by the eSTROOP as the second most demanding one. To allow for a break, the T1-weighted image is acquired next. Afterwards, the RS data is recorded, where the break during the T1-weighted image should also mitigate carryover effects from the previous task. The ERT isacquired last.

The fMRI implementation of the e-nBACK task will only consist of a 2-back and an additional 0-back condition as control organized in a mixed design [similar to (120)]. The conditions will be presented in eight blocks (four per condition) of 12 stimuli, where the pictures are shown for 2 s with 0.5 s between. Altogether, 96 stimuli will be shown. Blocks will be separated by baseline periods of 30 s. The whole task takes 8.5 min.

The fMRI adaptation of the eSTROOP task is taken from Alder et al. (121) respectively, Almdahl et al. (120): In short, 149 stimuli will be presented for 1 s each with jittered baseline periods of 3–5 s in an event-related manner. With additional baselines of 10 s at the beginning at end, the task will take ~13 min.

For the resting-state scan, subject will be told to lie as still as possible and let their mind wander. They are additionally shown the “Inscapes” video which was validated for fMRI acquisition and shown to significantly reduce in-scanner head movement (122). The acquisition takes 7 min.

In the fMRI version of the ERT, only the morphing faces will be used. A total of 42 stimuli will be presented in an event-related design, where the pictures are shown for a maximum of 2 s but should be interrupted via button press as soon as the subjects have identified the target emotion. After the stimulus and a short baseline of 1 s, the subjects have to select the target emotion out of six options. Stimulus-response pairs are interleaved with a jittered baseline of 5–10 s. The duration of the task strongly depends on the response times of the subjects but was ~10 min in previous investigations (123).

